### Safety analysis

All summaries and listings of safety data will be performed for the safety population. Frequencies of subjects experiencing at least one adverse event (AE) will be displayed by body system and preferred term according to MedDRA terminology. Detailed information collected for each AE will include: a description of the event, duration, whether the AE was serious, intensity, relationship to trial treatment, action taken, and clinical outcome. Summary tables will present the number of subjects observed with AEs and corresponding percentages. Additional subcategories will be based on event intensity and relationship to trial treatment. Analysis of device (CBVF)/graft (autologous bone) complaints will be analogously as far as possible.

### Withdrawal criteria

Patients can withdraw their consent without giving reasons for withdrawal at any time point of the study. The withdrawal will not have any negative consequences for the participant. The participation in this study may be discontinued:

1. upon the request of the sponsor for safety reasons

2. upon the request of a regulatory agency

3. if serious adverse events related to the therapy occurred

4. in case of non-compliance of participant

5. if participation in the trial would be of potential hazard to study participant´s health

6. if study participant will need a treatment which is specified in the protocol as exclusion criterium

7. if study participant becomes pregnant

Participants withdrawn from the study will not be replaced regardless of the reason for withdrawal. The investigator decides about the withdrawal of study until resolve of symptoms, but no longer than 6 months after the subject’s withdrawal from the trial.

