#### Evaluation and follow-up

Clinical evaluation and trial documentation consist of seven visits: screening (V1), intervention (V2) and five postoperative follow-up examinations ending with V7 after 26 weeks (Table 1).

**Table 1 T1:** Visit schedule

**Visit no**	**1**	**2**	**3**	**4**	**5**	**6**	**7**^ **§** ^
	**Day −7 – 0**	**Day 0**	**Day 1**	**Day 7**	**Week 6**	**Week 12**	**Week 26**
**Visit window**	**Screening**	**Day of surgery**	**± 1 day**	**± 3 days**	**± 1 weeks**	**± 2 weeks**	**± 3 weeks**
Informed consent	X						
Inclusion/Exclusion criteria	X						
Demography	X						
Patient employment status	X						
Medical history	X						
Weight and Height	X						
Physical examination	X						
Vital signs (pulse, blood pressure)	X						
Pregnancy test (women of childbearing potential)	X						
Concomitant medication/therapy	X	X	X	X	X	X	X
Evaluation of CT scan*	X						
Evaluation of X-ray findings*	X		X	X	X	X	X
Randomization	X						
Surgery** (autologous bone graft or treatment with CBVF***)		X					
Procedure information (type and amount of bone graft, hardware used, etc. - time of surgery)		X					
Adverse events	X	X	X	X	X	X	X
Device complaints		X	X	X	X	X	X
Clinical examination (pain, tenderness, warmth and swelling)				X	X	X	X
Documentation of treatments performed outside the trial center****							
Pain medication	X	X	X	X	X	X	X
SF-12v2TM	X			X	X	X	X
Pain (VAS)	X		X	X	X	X	X
End of the trial							X

*Computed tomography (CT) and X-ray assessments are performed as a clinical routine according to the standards of care. They will be not performed for the purposes of the study. **Surgical procedures are performed according to the standard of care. No surgical interventions will be performed for the purposes of the study. ***CBVF, CERAMENT™|BONE VOID FILLER. ****Continuous documentation by patient, when applicable. §These examinations should also be performed at the trial end visit in case the patient prematurely drops out of the trial.

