### Analysis populations

The intention to treat (ITT) population comprises all randomized patients, even if the planned surgery/surgeries did not take place. The modified intention to treat (mITT) population includes all randomized patients for which the primary endpoint could be assessed (that is, SF-12 PCS assessment is available both preoperatively and 26 weeks after surgery). Patients are eligible for the per protocol (PP) population, if they fulfill the following criteria: eligible for the mITT population, no violation of inclusion criteria, not meeting any exclusion criteria, trial treatment as randomized, time interval between Visit 2 (day 0, surgery) and Visit 7 (week 26): 22 to 30 weeks, absence of events with a strong effect on quality of life but definitely unrelated to the randomized study treatment (for example, new serious disease during post-operative follow-up, or accident).

The safety population comprises all randomized subjects who received trial treatment (autologous bone graft or Treatment with CBVF). In analyses of the safety population, subjects will be assigned to the treatment they actually received.

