### Assessments of safety

All adverse events (AE) and serious adverse events (SAE), including device-related events will be assessed und documented. Some AE may lead to secondary surgical interventions. According to the Good Clinical Practice (GCP) guidelines, secondary surgical interventions will be categorized as follows:

1. A revision is a procedure that adjusts or in any way modifies or removes part of the original implant configuration, with or without replacement of component. A revision may also include adjusting the position of the original configuration.

2. A removal is a procedure where the entire original system configuration is removed with or without replacement.

3. A reoperation is any surgical procedure at the involved site that does not remove, modify or add any components to the system.

4. A supplemental fixation is a procedure in which additional instrumentation not under study in the protocol is implanted (for example, supplemental placement of a rod/screw system or a plate/screw system).

5. All these secondary surgical interventions will be considered serious adverse events.

According to the Food and Drug Administration (FDA) definition, a device complaint is any written, electronic or oral communication that alleges deficiencies related to the identity, quality, durability, reliability, safety effectiveness, or performance of a device. All kinds of AEs (whether serious or non-serious) reported by the subject or detected by the investigator will be documented in the eCRF and in the patient´s medical records.

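### Withdrawal after a therapy-related serious adverse event can remove treatment failures from both confirmatory analyses, because outcome follow-up is not kept separate from withdrawal

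*Protocol article*

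**What the plan says.** All references are to the protocol article.

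- **Withdrawal criteria.** "The participation in this study may be discontinued" on seven grounds. The third is "if serious adverse events related to the therapy occurred". What ends is participation in the study, not only a treatment. "Participants withdrawn from the study will not be replaced regardless of the reason for withdrawal".
- **Assessments of safety.** Revision, removal, reoperation and supplemental fixation are defined, and then: "All these secondary surgical interventions will be considered serious adverse events". Where such an operation is judged related to the therapy, the third ground applies.
- **Analysis populations.** mITT requires that "SF-12 PCS assessment is available both preoperatively and 26 weeks after surgery". PP is nested in it ("eligible for the mITT population, no violation of inclusion criteria") and adds a visit window: "time interval between Visit 2 (day 0, surgery) and Visit 7 (week 26): 22 to 30 weeks". Among post-operative events that affect quality of life, PP removes only those clearly not caused by the study treatment.
- **Efficacy analysis.** PP is the primary set for PCS non-inferiority and mITT the primary set for pain. Supportive analyses of both endpoints are planned in mITT, PP and ITT, with multiple imputation for ITT.
- **Evaluation and follow-up, footnote to Table 1.** The Visit 7 examinations are also to be done at a trial end visit "in case the patient prematurely drops out of the trial".

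**The concern.** Both treatments are a single operation. Ending participation afterwards cannot take back the exposure; it only stops outcome collection. The patients this ground covers include those in whom the reconstruction or the graft harvest went wrong, whose week-26 PCS and pain matter most to the comparison.

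The PP definition is evidently meant to keep treatment-related failures in, since it removes only unrelated events. The withdrawal rule lets the same patients leave before the score that qualifies them is taken. The trial is open-label, and Source of bias concedes that assessors cannot be blinded, so a discretionary removal is made by people who know the arm. At stake is the validity of the non-inferiority claim if losses differ between arms, and to a lesser degree the pain comparison.

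**Working it through.** **Step 1. The path out of the analysis sets.** Therapy-related SAE, then possible end of participation, then an exit visit in place of week 26. Before week 22 the exit score is outside the PP window. Analysis populations does not say that an exit score counts as the week-26 score for mITT. Such a patient is then in neither primary set, and the supportive mITT and PP analyses carry the same requirement.

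**Step 2. The plan's own figures.** Margin 5, SD 10, true difference 0, one-sided 2.5%. With 64 per arm, SE = 10 × √(2/64) = 1.768, and the non-central t gives a power of 80.1%. So 128 reproduces. 128/0.95 = 134.7, or 136 in equal arms; that also reproduces.

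**Step 3. Bias.** Let f1 and f0 be the failure rates in the CBVF and control arms, D the PCS loss in a failure, and w the share of failures withdrawn.

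- All withdrawn (w = 1): bias = D × (f1 − f0).
- Share w withdrawn: the failure rate left in each arm is g(f) = f(1 − w)/(1 − f·w), and bias = D × [(f1 − f0) − (g(f1) − g(f0))].

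The documents give none of f1, f0, D or w; all are assumptions. For 8% v 3% and D = 15:

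- w = 1: 15 × 0.05 = 0.75.
- w = 0.5: g(0.08) = 0.04/0.96 = 0.0417 and g(0.03) = 0.015/0.985 = 0.0152, so bias = 15 × (0.05 − 0.0264) = 0.35.

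**Step 4. Type I error.** The true difference among all randomised patients is set at −5. The probability of claiming non-inferiority is the upper tail of a non-central t with 126 df and non-centrality bias/1.768, beyond 1.979.

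| CBVF v control | D | Withdrawn | Bias (points) | One-sided type I error |
|---|---|---|---|---|
| 5% v 5% | 20 | all | 0 | 2.5% |
| 8% v 3% | 15 | half | +0.35 | 3.9% |
| 8% v 3% | 15 | all | +0.75 | 6.2% |
| 5% v 10% | 15 | all | −0.75 | 0.9% |

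A simulation with 68 per arm and an unadjusted t interval (40,000 runs) gives 2.5%, 3.9%, 6.1% and 0.9% for the four rows. With every failure retained, the error is 2.5% to 2.6%.

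**Step 5. Scale.** 8% v 3% of 68 per arm is 5.4 + 2.0, about 7.5 patients or 5.5% of 136. The plan allows 5% PP ineligibility from all causes, so the fully withdrawn row already uses more than that allowance. As an outer bound, let all 8 patients of the allowance (136 − 128) be CBVF failures. That is 8/68 = 11.8% v 0%, a bias of 1.2 (D = 10) or 2.4 (D = 20), and a simulated type I error of 9.9% or 26.4%. This is a limit, not an expectation.

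**Step 6. Pain.** Under the planning distributions, the probability that a CBVF patient has more pain than a control, ties counted half, is 0.10 × 0.20 + ½ × (0.10 × 0.80 + 0.20 × 0.20) = 0.08. If 8 of 68 CBVF patients were failures with high VAS, it would be 8/68 + (60/68) × 0.08 = 0.19. Dropping them returns it to 0.08. Power is about 100% either way, so the estimate would move but the test result would not.

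**The case against.** **Withdrawal is discretionary.** A reader might infer that revised or reoperated patients leave the trial. The text does not say so. Participation may be ended, the event must also be related to the therapy, and Other endpoints has revisions, infections and hardware failures recorded throughout. A failure who stays and gives a week-26 score remains in mITT and, if otherwise eligible, in PP. This stands. The defect is a permitted loss, not a certain one.

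**The direction is not fixed.** A reader might infer that the rule biases the trial towards non-inferiority. That holds only if CBVF loses more failures, or worse ones. Background and rationale makes the reverse plausible: it lists donor-site nerve injury, haematoma, infection and pelvic fracture, and cites a trial of a different cement in which articular subsidence was commoner with bone graft. This stands too. A non-inferiority test must still be protected against the case in which the new material fails more often.

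**Safeguards exist.** The exit visit collects SF-12v2 and VAS, and an exit in weeks 22 to 26 could fall inside the PP window. The ITT analysis uses multiple imputation. It is tempting to say that imputation would give failures the values of completers, but the model is left to an SAP that is not shown and could use interim and exit scores. That criticism is not made here. What remains is that the ITT analysis is supportive and does not decide the claim, and that no analysis plan can recover a week-26 score that was never collected.

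**Follow-up after withdrawal.** The last sentence of Withdrawal criteria mentions up to 6 months after withdrawal. It is garbled, seems to concern resolution of symptoms, and does not establish SF-12v2 or VAS collection at week 26.

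**Conclusion.** The point holds as a conditional weakness: therapy-related failures who are withdrawn early can be lost from both confirmatory analyses, against the evident intent of the PP definition. For PCS the bias is about the difference in withdrawn-failure rates times the PCS loss, and its sign depends on which arm loses more. In the main scenario type I error is about 4% to 6% instead of 2.5%; with the rates reversed it falls below 2.5%. All rates, losses and withdrawn shares are assumptions, and the calculation uses SD 10 and an unadjusted comparison. For pain, a superiority test, the estimate may be distorted, but under the planning assumptions the conclusion would not change. The documents do not support the statement that the trial is biased towards non-inferiority. This should be fixed, and while the trial is recruiting, because missed week-26 scores cannot be collected later. It does not by itself invalidate the design.

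**What to change.** In Withdrawal criteria, separate withdrawal from outcome follow-up:

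- A therapy-related SAE, a secondary intervention, non-compliance or the need for an excluded treatment does not by itself end SF-12v2 and VAS collection. Collection continues to week 26, by post or telephone if needed, for every patient who still consents.
- The sponsor-safety, regulatory and hazard grounds stay as they are.

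In the Table 1 footnote, state that the exit visit is additional to the week-26 assessment and does not replace it. In Analysis populations, state that these patients stay in mITT and, if otherwise eligible, in PP.

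The change concerns data collection only and alters no care. It costs a short amendment and a few extra questionnaires: about seven or eight patients under the 8% v 3% assumption.

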### Assessments of safety

All adverse events (AE) and serious adverse events (SAE), including device-related events will be assessed und documented. Some AE may lead to secondary surgical interventions. According to the Good Clinical Practice (GCP) guidelines, secondary surgical interventions will be categorized as follows:

1. A revision is a procedure that adjusts or in any way modifies or removes part of the original implant configuration, with or without replacement of component. A revision may also include adjusting the position of the original configuration.

2. A removal is a procedure where the entire original system configuration is removed with or without replacement.

3. A reoperation is any surgical procedure at the involved site that does not remove, modify or add any components to the system.

4. A supplemental fixation is a procedure in which additional instrumentation not under study in the protocol is implanted (for example, supplemental placement of a rod/screw system or a plate/screw system).

5. All these secondary surgical interventions will be considered serious adverse events.

According to the Food and Drug Administration (FDA) definition, a device complaint is any written, electronic or oral communication that alleges deficiencies related to the identity, quality, durability, reliability, safety effectiveness, or performance of a device. All kinds of AEs (whether serious or non-serious) reported by the subject or detected by the investigator will be documented in the eCRF and in the patient´s medical records.

### Trial documentation and data collection

A detailed methodology for the data management in this trial will be documented in a data management plan (DMP) that will be dated and maintained by IZKS Mainz. The data acquisition will be performed using a web-based electronic case report form (eCRF). The investigator will enter the data via remote data entry (RDE) directly into the trial database, developed and maintained by IZKS Mainz. The system will be secured to prevent unauthorized access to the data or the system. The system provides the option of making exact data copies in legible paper form for review and audits. The investigator or a designated sub-investigator, following review of the data in the eCRF, will confirm the validity of each subject’s data by electronic signature or by signing a paper printout of all trial´s data. Checks for plausibility, consistency, and completeness of the data will be performed during and after data entry. After completion of data entry and if no further corrections are to be made in the database, the access rights will be taken away and the database will be declared closed and used for statistical analysis. All data management activities will be done according to the current standard operating procedures (SOPs) of IZKS Mainz. The names of the study participants and all other confidential information will be handled according to the medical professional secrecy and the regulations of the German Federal Data Protection Act. None of the patient-related information will become available to any person who is not directly involved in the medical treatment. During the clinical trial, subjects will be identified solely by means of an individual identification code. All trial results stored on a computer will be handled in accordance with the local data protection law in strictest confidence. For protection of these data, organizational procedures are implemented to prevent distribution of data to unauthorized persons. The appropriate regulations of data legislation will be fulfilled in its entirety. The subject will declare in the written consent to release the investigator from the medical professional secrecy to allow identification of subject’s name and/or inspection of original data for monitoring purposes by authorities and authorized persons.

### Source of bias

To reduce ascertainment bias, QOL and pain assessments will be performed by independent surgeons who will not be directly involved in the operative treatment of the patients. Furthermore, the assessments will be performed by persons with broad experience in treating trauma patients to determine whether or not events impacting QOL are really related to the treatment. The assessors will document all relevant events potentially impacting QOL and pain in the trial report. However, a consequent blinding of the assessors will not be feasible, since an additional wound will be obvious in all patients of the autologous bone graft group. Therefore, the method of assessment may be associated with an ascertainment bias, which cannot be avoided completely by the study design.

### Ethical issues

The procedures set out in the trial protocol, pertaining to the conduct, evaluation, and documentation of this trial, are designed to ensure that all persons involved in the trial abide by Good Clinical Practice [19] and the ethical principles described in the Declaration of Helsinki [20]. The trial is carried out in compliance with local legal and regulatory requirements. Prior to enrollment of the first subject, all ethical and legal requirements will be met by inclusive unreserved approval by institutional review boards. The final study protocol and the final version of the written informed consent form were already approved by the ethics committee of the University of Mainz, which is responsible for the site of the principal investigator. Medical experts have performed the critical assessments of risks and benefits in advance. Each site’s principal investigator ensures that all persons assisting with the trial are adequately informed about the protocol, the trial treatments, and their trial related duties and functions. Before being enrolled into the clinical trial, each subject must consent to participate after nature, scope, and possible consequences of the clinical trial have been explained to him or her in an understandable oral and written form. The subject must give consent in writing or orally in presence of an independent witness before randomization. Results of study will be published according to the most recent version of the Consolidated Standards of Reporting Trials statement [21].

## Discussion

Autogenous cancellous bone from the iliac crest is the most frequently used site for bone-graft harvest and remains to be the 'gold standard’ in reconstruction of bone defects and fracture non-unions in both metaphyseal and diaphyseal areas. The co-morbidities related to harvesting of autologous bone grafts are well documented [4,22-26]. Bone substitutes are used to avoid donor site problems associated with the harvest of the iliac crest bone graft. The clinical and functional outcome when comparing the use of autologous bone graft with the use of a bone graft substitute has been investigated in several studies [8,13,22,27]. However, the endpoints of those studies were mostly related to the ‘quality’ of the surgery performed. Good clinical outcome is directly related to the quality of the anatomical reduction of tibial plateau fractures [13,28]. Tibia plateau fractures have a high incidence of reduction loss when fixed without augmentation of the depressed articular fragments [4,29]. Actually, there are no studies that compare pain, QoL, and costs of care, which are all relevant endpoints related to the bone graft used. This necessitates the investigation of these outcomes in a sufficiently powered, prospective, randomized, controlled clinical trial. Current evidence, specifically reliable information from RCTs, is insufficient to counsel patients and their relatives with regard to the most convenient, efficient, and safe method to avoid prolonged pain and to restore a high level of quality of life and activity. As far as we know, the CERTiFy trial is the first randomized multicenter RCT that aims at generating conclusive evidence on the most appropriate way of treating tibia plateau fractures.

## Trial status

Recruiting

## Abbreviations

AE: adverse event; AIBG: autologous iliac bone graft; ANCOVA: analysis of covariance; AO: Arbeitsgemeinschaft Osteosynthese; CBVF: CERAMENT bone void filler; CE: Communautés Européennes; CERTiFy: CERAMENT treatment of fracture defects; CPC: calcium phosphate cements; CRF: case report form; CS: calcium sulfate; CT: computed tomography; DMP: data management plan; DRG: diagnosis related group; eCRF: electronic case report form; FDA: Food and Drug Administration; GCP: good clinical practice; HA: hydroxyl apatite; IFU: instruction for use; ITT: intention to treat; IZKS: Interdisziplinäres Zentrum für Klinische Studien Mainz; MCS: Mental Component Score; mITT: modified intention to treat; ORIF: open reduction and internal fixation; PCS: Physical Component Summary; PP: per protocol; Qol: quality of life; RCT: randomized controlled trial; RDE: remote data entry; SAE: serious adverse event; SAP: statistical analysis plan; SAS: statistical analysis system; SF-12v2: Short Form 12 Version 2; SF-12v2-PCS: Short Form 12 Version - physical component score; SF12v2-MCS: Short Form 12 Version 2 - mental component score; SF-36: Short Form 36 score; SOP: standard operating procedure; VAS: Visual Analog Scale.
